### Propensity score analysis

Another method we will use to model the probability of being referred for and obtaining CAM treatment is propensity score analysis [56,59,64-66]. Propensity scoring is an increasingly accepted collection of techniques to adjust for non-random selection among groups within observational studies. This approach is designed to remove most of the imbalance associated with the *measured *characteristics of cases allowing less biased estimates of treatment effect and other quantities linked with treatment (e.g., cost, quality of life). Propensity scores are designed to extract all of the relevant information from potential confounding variables. A consequence of this method is that two people in the same propensity stratum would be equally likely to receive the (CAM) treatment, after conditioning on all their known pre-treatment characteristics, which justifies an entirely conventional analysis. We will follow the modern literature on propensity scoring to use multiple models with different forms and assumptions, as this is the only way known to probe the validity of the resulting analyses. Table 3 includes a list of EMR variables available to us for this purpose.

**Table 3 T3:** Phase 1: Variables available from EMR for Clustering/Matching Patients

Types/duration of pain condition(s)
Pain severity
Comorbid conditions (e.g., depression, obesity)
Demographics (age, gender, race, marital status, employment status)
Receipt of pain-related disability compensation
Overall healthcare service use
Prescription medications received (e.g., short and long-acting opiates, sedatives, hypnotics, and antidepressants)
Pain-related procedures received (injections, imaging, and surgeries)
Pain-related visits (primary and specialty care including physical therapy)
ER/urgent care visits
Prior use of health insurance reimbursed CAM
Characteristics of primary care provider (e.g., degree [MD, DO, NP] frequency of CAM referrals, gender)

### Analysis of Matched Comparison Groups (MCG)

The third and primary approach we anticipate using to matching participants receiving A/C to suitable controls is the analysis of matched comparison groups. This approach is based on the notion that if, at a particular time, one can form a group of patients who are well-matched on prognostic factors, then within such a group decisions whether to use A/C cannot be based on the matching factors and must be weakly associated with unmeasured factors that are correlated with measured matching factors, thus tending to remove indication bias. If this type of matching were perfectly successful, then the absence of formal randomization would become irrelevant. In the analysis, one would compute treatment effects at the MCG level. Subsequent analysis would search for consistent results across similar MCGs, and in the presence of such similarity, accumulation of results would be applied to patient subpopulations. Formation of MCGs will be aided by the affinity clustering technique [54,67], which can be employed in large samples and has the advantage of identifying an "exemplar" patient whose variables represent those of the MCG members, thus making it possible to characterize MCGs at the analysis stage. Variables from the EMR include the patient characteristics and care variables delineated in Table 3. Available variables include many of those posited to be important factors in patients' decisions to use CAM therapies, as delineated in Figure 1 (Boxes A-C). Our large study patient pool study makes it possible to find MCGs of relatively closely matched CMP patients. We anticipate finding a large number of MCGs, each small and highly homogeneous. Outcomes will consist of various utilization measures, both generally and specific to CMP (see Table 4). We do not anticipate statistical significance at the MCG level due to their small size; rather, we intend to aggregate results across MCGs to investigate homogeneity of A/C effects and to relate the magnitude of A/C effects to MCG exemplar characteristics.

**Table 4 T4:** Phase 1: EMR-derived Clinical Outcomes

Overall use of health care services
Medication use (opiates, sedatives, hypnotics, and antidepressants)
Pain-related procedures (injections, imaging, surgery)
Pain-related visits (primary and specialty care)
Emergency room/Urgent care visits
Evidence of sleep problems
Adverse events attributed to conventional, acupuncture, or chiropractic care treatment for chronic musculoskeletal pain
Mood disorder diagnoses (depression, anxiety)

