### Event-stream methods

Management of longitudinal patient records is difficult because patients receive services in diverse ways. Unlike clinical trials in which all measures are collected in the same time frame, clinical records include patients who visit the health plan at different times for different services, each displaying a unique, idiographic "trajectory of care." For CMP patients, for example, this might include use of patient education, physical therapy, and opiate medications over a particular period of time. The event-stream method allows a richer description of patient care over time, more consistent with how patients receive services in routine care. The method defines an efficient data interface between the clinical/administrative databases and the analysis datasets [61,62]. Event-stream methods can be used to construct the types of variables that can then be used in a conventional analysis. This approach simplifies both the data extraction and statistical analysis and allows a richer array of variables for identifying matches or clusters of patients.

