### Outcome analyses

In identifying MCGs, we will use all CMP patient EMR data collected over a 5-year span (2006-2010). Patients must have a long enough duration of consecutive health plan membership to establish CMP eligibility and evaluate outcomes over the following year. To ensure maximum comparability, eligible patients must have clinical data available over a period when the A/C referral patterns were highly comparable. For each analytic approach, for each outcome measure, an A/C effect (comparing A/C and non-A/C patients) will be computed for each informative MCG. Table 4 shows the EMR-derived clinical outcomes that we plan to examine. We will employ conventional between-group estimates of the A/C effect measures. We anticipate, however, that there may be substantial heterogeneity of A/C effects across MCGs, so that it will be important to characterize where A/C has a beneficial effect, no effect, or an adverse effect. We will use both graphical methods as well as clustering of MCGs. We will also use explanatory linear models, usually ordinary regression, but potentially variants, depending on the specific type of outcome.

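### Phase 1's primary matched-group estimate states no adjustment for matching variables that still differ inside a group, so some measured confounding by indication can remain

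*Protocol article*

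**What the plan says.** The section Analysis of Matched Comparison Groups (MCG) sets the priority: "The third and primary approach we anticipate using to matching participants receiving A/C to suitable controls is the analysis of matched comparison groups". The groups come from affinity clustering around an exemplar patient. On the variables used it says: "Variables from the EMR include the patient characteristics and care variables delineated in Table 3". Table 3 has 12 rows, most of them holding several variables (the demographics row alone lists five). The Event-stream methods section adds that its technique "allows a richer array of variables for identifying matches or clusters of patients".

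On the quality of the groups, the MCG section says: "We anticipate finding a large number of MCGs, each small and highly homogeneous". More modestly, it also says: "Our large study patient pool study makes it possible to find MCGs of relatively closely matched CMP patients". Provided that a well-matched group can be formed, it reasons that "within such a group decisions whether to use A/C cannot be based on the matching factors".

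On estimation, the MCG section says "In the analysis, one would compute treatment effects at the MCG level", and Outcome analyses says "We will employ conventional between-group estimates of the A/C effect measures". The linear models mentioned there are called explanatory. The MCG section and EMR-related outcomes (Phase 3) describe relating the size of A/C effects to MCG characteristics, not adjusting inside an MCG. EMR-related outcomes carries the Phase 1 methods forward with the MCG as the unit of analysis and one-sample location tests for continuous measures. Patient-level variables with random MCG effects appear only there, and they are the patient-supplied ones.

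**The concern.** A within-group contrast removes confounding by a matching variable only as far as the group is tight on that variable. Clustering on many variables at once leaves spread on each. A/C and non-A/C members of one MCG can then still differ on the matching factors, on average in the direction in which those factors steer patients to A/C.

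Three things make this matter:

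- **The imbalance is real.** Table 2 shows clear differences in 2010 between patients with and without an A/C referral.
- **The matching variables predict the outcomes.** Five Table 3 rows (overall service use, medications, pain procedures, pain visits, emergency/urgent care visits) are earlier values of Table 4 outcomes.
- **Pooling does not help.** Combining many MCGs shrinks random error but not a systematic component, and Sample size considerations rests Phase 1 on precise estimation.

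The methodological aim is also exposed. The study compares EMR-only results with results augmented by patient data. If EMR variables are controlled only coarsely, patient-reported variables correlated with them could look informative merely because they absorb leftover EMR confounding.

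**Working it through.** The article gives no figure for MCG size, homogeneity or residual bias, so there is none to reproduce on this point.

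**Inputs from the article**

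- Pool: 122,896 patients (Sample size considerations).
- A/C share: 4816/(66768 + 4816) = 6.7% (Table 2; 2010 referral, used as a proxy for A/C use).
- Two or more pain types, 34.3% v 61.9%: standardised difference = (0.619 − 0.343)/√[(0.343×0.657 + 0.619×0.381)/2] = 0.276/0.480 = 0.57.
- Age, 57.4 (SD 15.5) v 52.3 (SD 14.8): (52.3 − 57.4)/√[(15.5² + 14.8²)/2] = −5.1/15.15 = −0.34.

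**Assumed, because the article does not say:** p = 12, 20 or 30 clustering variables and mean MCG size m = 10, 30 or 100.

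**Step 1: how tight can groups be?** For p independent, equally weighted normal variables and K groups, the average share of variance left within groups is at least K^(−2/p), whatever the clustering algorithm.

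| m | K = 122,896/m | p = 12 | p = 20 | p = 30 |
|---|---|---|---|---|
| 10 | 12,290 | 21% | 39% | 53% |
| 30 | 4,097 | 25% | 44% | 57% |

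For example, 12,290^(−2/12) = exp(−9.417/6) = 0.21.

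**Step 2: smaller groups are no way out.** With 6.7% A/C, a group of exactly 10 contains at least one A/C patient with probability 1 − 0.933^10 = 0.50. In simulation with mean size 10, only about 44% of MCGs held both an A/C and a non-A/C patient.

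**Step 3: what this does to the effect.** If A/C choice and outcome both depend roughly linearly on a confounder score, the A/C minus non-A/C difference in that score is proportional to its variance. The share of bias left is therefore about the share of score variance left within groups.

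This was simulated with N = 122,896, A/C share 6.7% and true A/C effect zero. K-means stood in for affinity clustering. Log-odds of 0.7 and an outcome correlation of 0.5 per SD of the score were assumed, with correlation between variables of 0 to 0.2. Within-MCG differences were pooled with weights equal to the number of A/C users. Share of the crude bias left in the unadjusted contrast:

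| Scenario | Share left |
|---|---|
| p = 12, m = 30, independent | 30% |
| p = 12, m = 30, correlated continuous | 20–32% |
| p = 12, m = 30, half binary | 8–33% |
| p = 20, half binary, m = 10 | 11–52% |
| p = 20, half binary, m = 30 | 16–61% |
| p = 20, half binary, m = 100 | 20–74% |
| p = 30, half binary, m = 30 | 23–73% |
| Score = equal-weighted sum of positively correlated variables | 1–6% |
| Only 3 to 6 variables | about 0–5% |

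Outside the last two rows the unadjusted difference was 0.03 to 0.25 SD. Adding the matching variables as covariates, with MCG effects, brought it to between −0.024 and +0.022 SD in every scenario.

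**The case against.** The strongest reply is that the text is more guarded than a quick reading suggests. The statement that decisions "within such a group decisions whether to use A/C cannot be based on the matching factors" follows an if-clause, homogeneity is anticipated rather than claimed, and matching is said only to tend to remove indication bias. A reader might infer that the plan asserts that confounding by the matching factors is gone. It does not.

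Second, Selection models and Propensity score analysis are planned alongside, and Multiple levels of analysis calls for conflicting results to be weighed. Outcome analyses says that an A/C effect is computed per informative MCG for each analytic approach, so confounder-modelling approaches may also feed MCG-level effects. A conventional between-group estimate does not strictly exclude covariates.

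Third, Table 3 lists variables that are available. Nothing commits the study to clustering on all of them with equal weight, and its utilisation measures are plausibly correlated, which lowers the effective dimension.

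Fourth, Phase 1 is preparatory, has no prespecified hypotheses, and is followed by a Phase 3 with patient-level adjustment.

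Much of this stands, and it limits both the size and the severity of the point. What remains is that the article states the expected homogeneity and the estimator for its primary approach, and ties no balance check or within-MCG adjustment to them. The parallel methods might disagree with the MCG result, but disagreement would not show which estimate is biased, nor would it correct the primary one.

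**Conclusion.** The point holds in a limited form. If MCGs are formed on a dozen or more weakly correlated variables, they cannot be both small and homogeneous on all of them. The primary Phase 1 estimate, as described, has no stated means of removing the measured confounding that is left.

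The variance bound rests on independent, equally weighted normal variables. The bias shares rest on the assumed confounding model, group sizes and variable counts. Across those assumptions the residual ran from near 0 to about 74% of the crude bias, and the documents do not say where in that range the study will fall.

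A reader might infer that the Phase 1 effect is certainly and heavily biased, with the same sign in every MCG, or that Phase 1 as a whole fails. The documents support none of these. The leftover has an expected direction on average, it can be negligible when few variables or one common factor drive the confounding, and other methods run in parallel. This is a recommended improvement, not a must-fix.

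**What to change.** In Outcome analyses, for each outcome, estimate the pooled A/C effect from a model with MCG effects, A/C and the patient-level Table 3 variables (or the propensity score plus a prognostic score). Choose a form suited to skewed or count utilisation outcomes. Derive the MCG-level effects, used to study heterogeneity, from covariate-adjusted outcomes.

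Report pooled within-MCG standardised differences for the Table 3 variables. In the MCG section, make the homogeneity expectation and the statement about A/C decisions inside a group conditional on that balance check. The balance itself cannot be stated before the data are analysed.

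MCGs and exemplars stay as planned, and the variables are already held. The cost is a little more analysis work and some reliance on the outcome model. The simulations do not show that adjustment works as well for skewed utilisation data. Unmeasured confounding remains in any case.

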### Outcome analyses

In identifying MCGs, we will use all CMP patient EMR data collected over a 5-year span (2006-2010). Patients must have a long enough duration of consecutive health plan membership to establish CMP eligibility and evaluate outcomes over the following year. To ensure maximum comparability, eligible patients must have clinical data available over a period when the A/C referral patterns were highly comparable. For each analytic approach, for each outcome measure, an A/C effect (comparing A/C and non-A/C patients) will be computed for each informative MCG. Table 4 shows the EMR-derived clinical outcomes that we plan to examine. We will employ conventional between-group estimates of the A/C effect measures. We anticipate, however, that there may be substantial heterogeneity of A/C effects across MCGs, so that it will be important to characterize where A/C has a beneficial effect, no effect, or an adverse effect. We will use both graphical methods as well as clustering of MCGs. We will also use explanatory linear models, usually ordinary regression, but potentially variants, depending on the specific type of outcome.

#### Multiple levels of analysis

In clinical trials, it is appropriate to pre-specify the main analyses; however, in clinical non-intervention research, the reverse is the case. As emphasized in Guo and Fraser [60], because each analytic approach has its own strengths and weaknesses, it is essential to carry out a multiplicity of different analyses and assess their potentially conflicting results in the context of broad knowledge about clinical processes and patient behaviors. This virtually guarantees that reports of research results from non-intervention studies will be more lengthy and complex than their clinical trial counterparts.

### Sample size considerations

Unlike an RCT, at this stage of EMR-based research we do not have simple, prespecified hypotheses to test. Furthermore, in the light of the desirability of carrying out multiple types of analyses with different endpoints and analysis variants, it is not feasible to make standard sample size computations. Instead, study justification rests on the very large pool of eligible patients (122, 896 health plan members with EMR-identified CMP from 2006 to 2010) and analysis relies on precise estimation of potential effects, rather than on statistical decision-making. Moreover, part of the purpose of an EMR-based study is to portray the variability of response patterns at the individual patient level (as opposed to an average result for the entire sample) to the extent that this is observable. Here again, statistical decision-making does not seem to be an optimal approach.

### Survey of A/C use by CMP patients

Our first-step Phase 1 analyses are confined to variables available in the EMR, which we will use to develop a broadly replicable and efficient approach to evaluating A/C impact. However, patients may be using A/C and other CAM therapies in ways not visible within the EMR. Similarly, there may be patient characteristics contributing to the decision to use A/C therapies that are also not readily visible in the EMR. To address these issues, we will identify patients whose EMR records suggest the presence of CMP within the past two years; we will then invite them to complete a survey identifying current and prior out-of-plan A/C use and use of related treatments/practices. A copy of the survey is available from the first author. We will then replicate the Phase 1 procedures (described above) with the enhanced data set including only those individuals who responded to the survey. This will allow us to evaluate the robustness of our findings by comparing the MCG characteristics identified using only EMR data with those identified in this augmented data set. Additional insights and characteristics predictive of out-of-plan use will help guide sampling of CMP participants for the focus groups in Phase 2, as well as the MCG design for matching participants in Phase 3. Data on out-of-plan use will be most accurate for current use patterns, which are most important for Phases 2 and 3. There will still be "noise" in this data for two reasons: first, not all CMP patients will respond to the survey; second, retrospective self-reporting may not allow us to determine with certainty whether self-care practices or out-of-plan CAM use preceded receipt of covered A/C care. Nonetheless, reporting such practices indicates a patient's general proclivity to seek CAM services or engage in self-care practices to address health concerns. Information on this tendency may enhance our interpretation of patient decision-making and outcomes.

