## Discussion

We expect that successful completion of this study will provide an evaluation of the outcomes--from the perspectives of patients, providers, and health services utilization--associated with the real-world use of A/C services. By comparing the results of the EMR-only analyses with the more comprehensive results available in Phase 3, we will be able to identify the strengths and weaknesses of EMR-alone analyses and potentially identify the most critical additional data needed. We further anticipate that the trio of EMR-based analyses, qualitative assessment, and prospective cohort studies will provide a clearer understanding of the decision-making processes behind the use of A/C for CMP; these will also provide a transportable methodology that can be applied to other health care settings, CAM treatments, and clinical populations.

With regard to advancing our understanding of patients' use of CAM in everyday practice settings, much CAM research to date has focused narrowly on "early adopters" (those likely to use CAM services regardless of barriers [117]). Yet within our cohort, cost and access barriers are substantially reduced, allowing us to study other factors (see Figure 1) influencing A/C care receipt and outcomes and to develop a comprehensive characterization of A/C use patterns and outcomes in patients with increasing access to such CAM services. An important goal of this study is to clarify how CMP patients use A/C compared to conventional care (to augment or replace it), when and why patients disclose A/C use to allopathic providers, and how such practices may vary by patient characteristics. Our mixed methods approach will help us develop a better understanding of the process behind the decision to initiate (patients), recommend (allopathic providers), and continue (patients and providers) A/C care for the treatment of CMP. Finally, studying this in everyday treatment settings allows us to consider the range of services received in A/C care (e.g., needling or spinal manipulation vs. whole systems-based care) and variation by characteristics of the CMP patient and/or A/C provider.

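### The Phase 1 survey robustness check changes the variables and the patients together, so it cannot show what the survey data add unless EMR-only is also run in the responders

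*Protocol article*

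**What the plan says.** Three places in the Protocol article define the comparison.

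- **EMR-only run.** Under Outcome analyses: "In identifying MCGs, we will use all CMP patient EMR data collected over a 5-year span (2006-2010". Sample size considerations gives the pool as "122, 896 health plan members with EMR-identified CMP from 2006 to 2010". The survey section describes this run as follows: "Our first-step Phase 1 analyses are confined to variables available in the EMR".
- **Augmented run.** Under Survey of A/C use by CMP patients, the invitation goes to a narrower set: "we will identify patients whose EMR records suggest the presence of CMP within the past two years". Then: "We will then replicate the Phase 1 procedures (described above) with the enhanced data set including only those individuals who responded to the survey".
- **Contrast.** The same section says robustness will be evaluated by "comparing the MCG characteristics identified using only EMR data with those identified in this augmented data set".

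That section names two limitations and calls both noise. One is that not every patient will respond. The other is that "retrospective self-reporting may not allow us to determine with certainty whether self-care practices or out-of-plan CAM use preceded receipt of covered A/C care".

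**The concern.** A check meant to show whether findings hold up when survey data are added should change only the data. Here the second run also changes who is analysed. If the MCGs look different, the reader cannot tell whether the survey variables mattered or whether responders are simply other patients. If the MCGs look alike, two real shifts may have offset each other.

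Non-response to a questionnaire about CAM use may well be related to CAM use, which is the exposure under study. It would then act as a systematic shift and not as noise.

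Timing is a secondary matter. Phase 1 treats data before the virtual enrollment date as baseline. If out-of-plan use of unknown date enters the re-clustering, some of it may have followed the A/C care being evaluated.

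**Working it through.** The article declines a standard sample size computation for Phase 1 and gives no figure for this check, so there is nothing to reproduce. The check sets the two runs side by side and then splits the contrast.

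**Step 1. What differs between the runs**

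| Feature | EMR-only run | Augmented run |
|---|---|---|
| Variables | EMR | EMR plus survey |
| Eligibility window | CMP in 2006-2010 | CMP in the past two years |
| People | All CMP patients with enough membership | Survey responders |
| Sample | From a pool of 122,896 | Smaller; response rate not given |

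Four features change. Sample size and window matter in their own right, because both can alter the clusters that a clustering method finds.

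**Step 2. Identity**

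Let E(full) be any result of the EMR-only run in the full cohort, E(resp) the same EMR-only procedure in responders, and A(resp) the augmented run in responders.

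A(resp) - E(full) = [E(resp) - E(full)] + [A(resp) - E(resp)]

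The first bracket is the population term: response selection, window and sample size. The second is the added-data term. The article describes E(full) and A(resp) but not E(resp), so only the sum is seen. A larger sample does not separate the two.

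**Step 3. Illustration**

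Every input in this step is an assumption. There are 1,000,000 simulated patients, one EMR covariate, one survey-only binary variable (prevalence 0.4) and one unadjusted effect modifier (prevalence 0.5) that may drive response. Response rates come out at 31% to 35%. The result tracked is a linearly adjusted A/C effect.

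| Assumed case | E(full) | E(resp) | A(resp) | Planned contrast | Population term | Data term |
|---|---|---|---|---|---|---|
| A. Survey variable not a confounder, moderate selection | -0.894 | -1.023 | -1.023 | -0.129 | -0.129 | 0.000 |
| B. As A, strong selection | -0.902 | -1.146 | -1.146 | -0.245 | -0.245 | 0.000 |
| C. Strong confounding, no selection | -0.660 | -0.649 | -0.891 | -0.231 | +0.011 | -0.242 |
| D. Terms in opposite directions | -0.259 | -0.176 | -0.267 | -0.008 | +0.083 | -0.091 |

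Differences were taken before rounding, so the last digit may be off by one.

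B and C give nearly the same planned contrast for opposite reasons. D looks robust although adding the survey variable moves the estimate by -0.091. With E(resp) available, the data term is recovered in each case. Across the other settings run, it was about -0.06 at moderate confounding and -0.24 to -0.25 at strong confounding, and hardly changed with the strength of selection.

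The illustration concerns an effect estimate, while the article's stated target is MCG characteristics. It shows how the contrast can mislead, not how far cluster characteristics would move. The identity in step 2 holds for any numerical summary.

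**The case against.** The strongest reply is that a robustness check may vary sample and variables together, that the article never says a difference will be credited to the survey data, and that an article condenses a fuller plan. It also does not say in one sentence that the EMR-only side is the full cohort. The section on multiple levels of analysis expects many analyses, so a responder-only EMR run is not ruled out. The first part stands: no attribution is stated. But the article presents this contrast as what allows robustness to be judged, and the contrast is hard to interpret whichever way it turns out. That is a choice of comparison, not an omitted detail.

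Four stronger readings are tempting, and the documents do not support them.

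- **That a stated study goal fails.** The Background gives two goals: who benefits from A/C, and an exportable method. Whether EMR data suffice is a component of the second, not a goal by itself.
- **That the Phase 3 claim fails too.** The Discussion ties the question to Phase 3 ("By comparing the results of the EMR-only analyses with the more comprehensive results available in Phase 3"), and the Phase 3 section on EMR-related outcomes already applies the EMR-alone strategy in the Phase 3 sample and then adds patient-supplied variables. That is the same-sample design asked for here.
- **That the flawed contrast steers Phase 3 matching.** The survey section says Phase 3 matching is guided by what predicts out-of-plan use, which comes from the responders' own answers.
- **That the re-clustering will match on a consequence of A/C.** The survey is not shown, it asks about both current and prior use, and the article does not say which items enter the clustering. This is a possibility only.

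**Conclusion.** The point holds for the Phase 1 survey check. As described, it mixes the contribution of the survey variables with response selection, the two-year window and the smaller sample. The size is unknown, because neither the response rate nor any difference between responders and non-responders is given.

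The conclusion rests on reading the EMR-only side as all 2006-2010 CMP patients. The Outcome analyses section and the first-step wording make that the plain reading, and no other comparator is mentioned. If the full protocol already has an EMR-only run restricted to responders, the main point falls away and only the timing caution remains.

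The consequence is limited to how an exploratory Phase 1 analysis can be interpreted.

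**What to change.** 1. Add a bridging run: repeat the Phase 1 procedures on EMR variables alone in the same responders.
2. Attribute to the survey data only the difference between EMR-only and EMR-plus-survey within responders.
3. Report the difference between the full-cohort and responder EMR-only runs as selection, noting that it also carries the window and sample size. Describe responders and non-responders on EMR variables.
4. Keep survey items that cannot be dated before the virtual enrollment date out of the primary re-matching, or use them only in a sensitivity run.

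The bridging run reuses existing code and data. Sorting items by date takes somewhat more analyst time, and for some items the order may prove undeterminable, which is why item 4 allows a sensitivity run. No new data collection is needed.
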